## Abstract

**Introduction:**

Pulmonary vein (PV) isolation has been shown to reduce atrial fibrillation (AF) burden and symptoms in patients. However, to date previous studies have been unblinded raising the possibility of a placebo effect to account for differences in outcomes.

**Hypothesis & Methods:**

The objective of this study is to compare PV isolation to a sham procedure in patients with symptomatic AF. The SHAM‐PVI study is a double blind randomized controlled clinical trial. 140 patients with symptomatic paroxysmal or persistent AF will be randomized to either PV isolation (with cryoballoon ablation) or a sham procedure (with phrenic nerve pacing). All patients will receive an implantable loop recorder. The primary outcome is total AF burden at 6 months postrandomisation (excluding the 3 month blanking period). Key secondary outcomes include (1) time to symptomatic and asymptomatic atrial tachyarrhythmia (2) total atrial tachyarrhythmia episodes and (3) patient reported outcome measures.

**Results:**

Enrollment was initiated in January 2020. Through April 2023 119 patients have been recruited. Results are expected to be disseminated in 2024.

**Conclusion:**

This study compares PV isolation using cryoablation to a sham procedure. The study will estimate the effect of PV isolation on AF burden.

## INTRODUCTION

1

Atrial fibrillation (AF) is the most common cardiac arrhythmia with an 8.5% prevalence in men and 7.1% prevalence in women over the age of 55.^1^ It is estimated there are 8.8 million adults with AF in the European Union.^1^

Catheter ablation has been shown to reduce the occurrence of AF and improve quality of life and symptoms in patients with symptomatic AF when compared to medical therapy, for example the CABANA study showed significant improvements in quality of life and symptoms.^2^, ^3^ However previous trials involving catheter ablation have not been blinded raising the possibility of a placebo effect accounting for the differences in outcomes.

The ORBITA trial (Percutaneous intervention vs placebo in angina patients) and SYMPLICITY HTN‐3 (renal denervation vs sham procedure in resistant hypertension) trials have shown that placebo controlled trials for device therapy are safe and feasible. Indeed both trials showed a placebo effect in device therapy, which had not been accounted for previously.^4^, ^5^

This study is an investigator led randomized double blind trial comparing catheter ablation to sham therapy in patients with symptomatic persistent or paroxysmal AF.

## METHODS

2

The objective of this study is to evaluate the effectiveness of pulmonary vein (PV) isolation vs a sham procedure in patients with symptomatic persistent or paroxysmal AF. The null hypothesis predicts that PV isolation has no effect on AF burden compared to a sham procedure.

Paroxysmal AF (PAF), also termed intermittent AF, is defined as any episode of AF that terminates spontaneously or with intervention in less than 7 days.^6^ Persistent AF is defined as any continuous AF episode that is sustained beyond 7 days.^6^ Long‐term persistent AF is defined as any continuous AF episode lasting more than 12 months in duration and patients in permanent AF are defined as such when the clinician and patient make a joint decision to stop further attempts at maintaining sinus rhythm.^6^

The major inclusion criteria for the study comprise patients with symptomatic paroxysmal or persistent AF despite at least one antiarrhythmic drug (AAD Type I or III, including β‐blocker and AAD intolerance). The major exclusion criteria include long‐term persistent AF (any continuous AF episode lasting more than 1 year), prior left atrium (LA) catheter or surgical AF ablation, patients with other arrhythmias requiring ablative therapy, LA ≥ 5.5 cm and ejection fraction (LVEF) less than 35% (Table 1). Any patient enrolled in the study who withdraws their consent will be removed from the study, but at enrollment their consent will be sought to use the data already recorded. For participants who are lost to or do not attend follow‐up, data shall be obtained from hospital medical records and/or primary care records where possible.

**Table 1 clc24066-tbl-0001:** Inclusion and exclusion criteria.

Inclusion criteria
Age greater than or equal to 18 years
Symptomatic paroxysmal or persistent atrial fibrillation despite at least one antiarrhythmic drug (AAD Type I or III, including β‐blocker and AAD intolerance)
Referred for catheter ablation
Exclusion criteria
Long term persistent AF (any continuous AF episode lasting more than 1 year)
Prior left atrium catheter or surgical atrial fibrillation ablation
Patients with other arrhythmias requiring ablative therapy
Left atrium (LA) ≥ 5.5 cm
Left ventricular ejection fraction (LVEF) less than 35%
Any cardiac surgery or percutaneous coronary intervention (PCI) within 3 months before enrollment.
Awaiting cardiac surgery or PCI
Myocardial infarction within 3 months before enrollment
Stroke or transient ischemic attack (TIA) within 3 months before enrollment
Unstable angina
Any significant congenital heart defect corrected or not (including atrial septal defects or PV abnormalities) but not including patent foramen ovale
Any condition contraindicating chronic anticoagulation
Any untreated or uncontrolled hyperthyroidism or hypothyroidism
Severe chronic kidney disease (stage V, requiring or almost requiring dialysis, glomerular filtration rate (GFR) < 15 ml/min)
Patients with prosthetic valves
Pregnant or breastfeeding women
Medical conditions limiting expected survival to <1 year
History of claustrophobia or panic attacks

Outcome measures will be evaluated at 3 months postrandomisation and 6 months postrandomisation (Table 2). The first 3 months postrandomisation will constitute the blanking period. The primary outcome measured is the comparison of AF burden using continuous monitoring at 6 months post‐randomisation between the intervention group and control group. Key secondary outcomes include time to atrial tachyarrhythmia and patient reported outcome measures (Table 3).

**Table 2 clc24066-tbl-0002:** Schedule of interventions and assessments.

	Enrollment	Day 0/Procedure day	3 Months	6 Months
Consent	X			
AF symptom review	X		X	X
Clinical examination	X		X	X
Medication review	X		X	X
Adverse event review		X	X	X
Echo (if not performed in last 12 months)	X			
ECG	X	X	X	X
Questionnaires		X	X	X
ILR implantation (if not already implanted)	X			
ILR interrogation		X	X	X
Procedure (ablation/sham)		X		
Blinding assessment		X	X	X

Abbreviation: ILR, implantable loop recorder.

**Table 3 clc24066-tbl-0003:** Secondary outcomes.

Time to any atrial tachyarrhythmia stratified by length of episode (more than 30 s/more than 7 days)
Time to symptomatic atrial tachyarrhythmia
Number of atrial tachyarrhythmia episodes (symptomatic and asymptomatic) in the follow‐up period in each group stratified by length of episode (more than 30 s/more than 7 days)
Comparison of medical treatment in each group in the follow‐up period
Comparison of health related quality of life in each group (SF‐36)
Comparison of AF specific quality of life score between each group; Atrial Fibrillation Effect on Quality‐of‐Life (AFEQT) Questionnaire, Mayo AF Symptom Inventory (MAFSI) and EHRA class
Comparison of unscheduled use of health care services during follow‐up
Procedure related complications/adverse events between each group

## METHODS

3

This is a double blind, randomized sham controlled study commenced in December 2019 (Figure 1). The committee members are listed in the Supporting Information Material (Supporting Information: Appendix 1). Patients meeting the inclusion and exclusion criteria are recruited from hospitals within East Sussex Healthcare NHS Trust and Mid and South Essex NHS Foundation Trust (Supporting Information: Appendix 2). 140 patients meeting the inclusion and exclusion criteria will be recruited. Ethical approval has been obtained from the West Midlands—South Birmingham Committee (19/WM/0361).

**Figure 1 clc24066-fig-0001:**
[figure not shown]
The SHAM PVI study timeline. One hundred fourty patients will be enrolled and randomized in a 1:1 ratio to receive cryoablation or a sham procedure. All patients will receive an ILR. Outcomes will be assessed at 3 and 6 months post‐randomisation with the first 3 months constituting the blanking period. DCCV, Direct current cardioversion; ILR, implantable loop recorder.

Following recruitment and baseline measurements, all patients will undergo an implantable loop recorder (ILR) implantation (Reveal LINQ, Medtronic Inc.) if this has not been inserted previously. It is recommended the ILR be inserted at least 2 weeks before the main procedure day or on the main procedure day dependent on covid‐19 restrictions.

### Implantable loop recorder insertion

3.1

A Medtronic Reveal LINQ loop recorder will be inserted as per manufacturer guidelines at study enrollment. The device settings will be optimized to record all AF episodes longer than 2 min (Supporting Information: Table 1). The device is able to wirelessly transmit all ECG recordings and activated episodes on a daily basis. The AF algorithm has a reported sensitivity of 97.4% and positive predictive value of 73% however all recordings will be manually reviewed by a 3‐person adjudication committee blinded to patient group.^7^, ^8^

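### Two secondary outcomes use a 30 s lower class, but the loop recorder is set to record AF only above 2 min, so the label does not match the data

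*Protocol article*

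**What the plan says.** All statements are in the protocol article.

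- **Outcome definitions (Section 2, Table 3).** The first row is "Time to any atrial tachyarrhythmia stratified by length of episode (more than 30 s/more than 7 days"). The episode-count row covers episodes with and without symptoms "in the follow‐up period in each group stratified by length of episode (more than 30 s/more than 7 days"). A separate row, "Time to symptomatic atrial tachyarrhythmia", gives no duration.
- **Recording (Section 3.1).** The recorder setting is: "The device settings will be optimized to record all AF episodes longer than 2 min". Details are referred to a supporting table that is not shown. The section adds: "The device is able to wirelessly transmit all ECG recordings and activated episodes on a daily basis".
- **Adjudication (Section 3.1).** The article says that "all recordings will be manually reviewed by a 3‐person adjudication committee blinded to patient group".
- **Primary outcome (Section 2).** This is the "comparison of AF burden using continuous monitoring at 6 months post‐randomisation between the intervention group and control group".
- **Standing of the outcomes.** The Abstract names time to symptomatic and asymptomatic arrhythmia, and total episodes, among the key secondary outcomes.

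**The concern.** The lower class of two outcomes starts at a duration that the described instrument is not set to record. An AF episode of, say, one minute meets the Table 3 definition but lies below the Section 3.1 setting. If the plan is followed as written, the time-to-event result and the episode count will carry a 30 s label although the data behind them start at 2 min. A reader comparing these results with another study that really used 30 s would be comparing unlike quantities. Episodes that were never stored cannot be recovered later by the analysis plan or by adjudication.

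**Working it through.** **1. The two thresholds side by side**

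| Item | Duration | Source |
|---|---|---|
| Lower class, time to any atrial tachyarrhythmia | > 30 s | Table 3 |
| Lower class, number of episodes | > 30 s | Table 3 |
| Upper class, both outcomes | > 7 days | Table 3 |
| Time to symptomatic atrial tachyarrhythmia | none stated | Table 3 |
| Recorder setting for AF | > 2 min = 120 s | Section 3.1 |

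Ratio of recording to outcome threshold: 120 / 30 = 4.

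**2. Is there another route for episodes of 30 s to 2 min?**

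- *Another continuous monitor:* none is described.
- *Patient-activated recordings:* Section 3.1 mentions activated episodes without a duration. They may catch some short episodes that the patient feels, but not unnoticed ones, which the count outcome expressly includes.
- *Visit ECGs:* Table 2 schedules them at enrollment, on the procedure day and at 3 and 6 months. Each shows the rhythm at one moment, so a short episode is found only by chance.
- *Adjudication:* it reviews recordings. It can remove false detections but cannot add what was not stored.

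None of these captures the 30 s to 2 min band systematically.

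**3. Direction of the error, for AF seen through the automatic detector**

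Count: N(>30 s) = N(30–120 s) + N(>120 s). The recorder delivers N(>120 s), which is at most N(>30 s). If p is the share of qualifying episodes in the 30–120 s band, the reported count is (1 − p) times the defined count. The documents give no distribution of episode lengths, so p could lie anywhere from 0 towards 1.

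First event: T(>30 s) is the earlier of the first episode in the band and the first episode over 120 s. The recorder delivers the latter, which is equal or later. The delay is zero in any patient whose first event already exceeds 2 min.

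Comparison of arms: the ratio of reported counts equals the ratio of defined counts times (1 − p in the ablation arm) / (1 − p in the sham arm). It is unchanged if p is equal in the two arms. The documents say nothing on whether it is.

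**4. Effect on the primary outcome**

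Assume 90 days of monitoring after the blanking period.

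- Monitored time: 90 × 1,440 = 129,600 min.
- One percentage point of burden: 0.01 × 129,600 = 1,296 min.
- Missed episodes of at most 2 min needed for one point: at least 1,296 / 2 = 648, or 648 / 90 = 7.2 per day.

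Section 3.8 plans on a difference of 25 points (50% against 25%), so the effect on burden is negligible.

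**5. Sample size**

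With a difference of 25, SD 48, two-sided 0.05 and 80% power, the two-sample t-test needs 58.84, so 59 per arm and 2 × 59 = 118 in total, as Section 3.8 states. Neither duration threshold enters that calculation.

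**The case against.** The best case against the point is that this is a small labelling matter. Every AF episode over 2 min is also over 30 s, so the recorder does deliver most of what the definition asks for, and the class of more than 7 days is untouched. Both arms carry the same device, patients and follow-up staff are blinded, and adjudication is blinded. In the preliminary data 84 of 105 patients (80%) have persistent AF, so very short episodes may seldom supply the first event. The outcomes concern atrial tachyarrhythmia, which is wider than AF, and the supporting settings table may hold a different limit for non-AF rhythms.

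Most of this stands and limits the point, but none of it reconciles the two durations. The setting for AF is printed in the main text, and a separate limit for other rhythms would not alter it.

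A reader might also infer more than the documents support:

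- *That the outcomes cannot be measured at all.* Only the 30 s to 2 min band is lost.
- *That both time-to-event outcomes conflict with the setting.* The symptomatic one states no duration, so it does not.
- *That there is a double threshold, 30 s for felt and 2 min for unfelt arrhythmia.* The article does not say that activated or ECG strips count at 30 s.
- *That the comparison of arms is biased.* This would require the missed share to differ between arms, and nothing in the article shows that.

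**Conclusion.** The inconsistency is real and confined to the lower class of two secondary outcomes. As written, they would be reported as arrhythmia over 30 s while the systematic data cover AF over 2 min. Counts would be too low and first-event times equal or too late. The amount cannot be computed because the documents give no distribution of episode lengths.

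The conclusion rests on two assumptions: that Section 3.1 means what it plainly says for AF, and that no continuous monitor other than the loop recorder is used. The primary outcome and the sample size are not at risk. Severity is moderate: the two outcomes are named as key secondary and are mislabelled as written, but no effect on the main conclusion of the trial is shown.

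**What to change.** Reconcile Table 3 with Section 3.1, and carry the same wording into the analysis plan before database lock:

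- In the rows for time to any atrial tachyarrhythmia and for number of episodes, replace the lower class by adjudicated episodes longer than 2 min detected by the loop recorder. Keep the class of more than 7 days.
- For these two outcomes only, list shorter patient-activated or ECG-documented episodes separately and do not add them to the count or use them as first events.
- Leave the symptomatic time-to-event outcome unchanged. It has no duration limit, and short activated recordings may be valid events there.
- If the supporting settings table gives a different limit for non-AF atrial tachyarrhythmia, state it next to the 2 min AF limit.

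The cost is a wording change. It needs no new data and alters neither the sample size nor the primary analysis. The downside is that these results lose the 30 s label and can no longer be set directly beside studies that use it; the recorder setting as described does not support that label in any case.

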### Pre‐procedure medication management

3.2

AADs will be discontinued five half‐lives (up to 5 days) before the procedure, except for Amiodarone, which will be discontinued 8 weeks before procedure day. Procedures will be performed on uninterrupted anticoagulation. Patients will remain on anticoagulation for the duration of the study.

### Randomization

3.3

Participants will be randomly assigned in a 1:1 ratio to undergo either catheter ablation ± DCCV (if in AF) or a sham procedure ± DCCV (if in AF). A computerized central blocked randomization design will be generated and stratified according to type of AF (paroxysmal/persistent). Randomization blocks will be performed with “ralloc,” Stata's randomization process v.16.0. The block sizes will not be disclosed to study investigators, to ensure concealment.

The randomization sequence and study‐group assignments will be prepared and placed in sequential numbered sealed, opaque envelopes by a fellow with no involvement in the execution of the trial. The envelopes will be kept securely by a sponsor administrator not involved in the conduct of the study.

The allocation will remain concealed until after sedation has been achieved at the time of the procedure.

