### Sedation and blinding

3.4

During each procedure patients will be given over‐the‐ear headphones playing music to prevent hearing of communication between cath‐lab staff. Patients will then be sedated during the procedure using opiates and benzodiazepines and have eye coverings if necessary. After the procedure, all nursing staff, physicians and other health care professionals performing the procedure will have no further contact with the patient during follow‐up. Health care professionals or research staff involved in the patient care post‐procedure and during follow‐up will be blinded to the treatment strategy (Supporting Information: Appendix 3 and Supporting Information: Figure 1).

Participant blinding will be assessed at the time of discharge, 3 months and at 6 months follow‐up. Participants will be asked to guess one of the following: (1) ablation, (2) placebo, (3) Don't know. Participants will also be asked to state the certainty of their answers on a grade scale of 1−5 with 5 being most sure.

Staff members will also be asked at discharge, 3 months and at 6 months follow‐up to guess the patient treatment allocation.

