### Cryoablation procedure

3.5

At the beginning of the procedure x2 femoral venous access will be achieved using ultrasound guidance. If the patient is in AF then DCCV will be undertaken to cardiovert to sinus rhythm.

A multipolar catheter will then be placed in the coronary sinus. The LA will then accessed via trans‐septal puncture or patent foramen ovale. Following left atrial access, IV heparin will be administered as sequential boluses maintaining activated clotting time more than 300 s. Thereafter the TS sheath will be exchanged with a steerable 15 Fr sheath (Flexcath, Medtronic). A 28 mm cryoballoon catheter (Arctic Front Advance, Medtronic) will be advanced through the steerable sheath into the LA with a guide wire or the Achieve mapping catheter in the central lumen.

The cryoballoon will be positioned in the ostium of each PV using fluoroscopic guidance and contrast injection with minimal or no dye leak on injection after inflation.

Before ablation of the right PVs, the multipolar catheter will be placed in the right subclavian vein to pace the right phrenic nerve (10–20 mA at 1.0–2.0 ms pulse width at a cycle length of 1000 ms). Ablation will be immediately terminated upon any perceived reduction in the strength of diaphragmatic contraction.

Cryoablation in each PV will be applied for a minimum duration of 180 s and maximum duration of 240 s. If the temperature has not reached −40 degrees by 60 s then this will be deemed to be an ineffectual ablation and the ablation will be stopped and the balloon repositioned. A further 2 attempts at ablation will be allowed. Entrance and exit block will also be confirmed and if the operator fails to isolate the PV (excluding common ostia) after a minimum of 3 attempted cryoballoon applications then focal ablation with the 8 mm cryocatheter (Freezor Max) targeted to sites of LA‐PV breakthrough will be permitted at operator discretion.

At the end of the procedure once sheaths have been removed all patients will have a three‐way stopcock suture to achieve haemostasis.

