### Sham procedure

3.6

After x2 venous access has been achieved using ultrasound guidance, DCCV will be undertaken if the patient is in AF. A 5‐Fr pacing catheter will then be placed at the right subclavian vein to pace the phrenic nerve (10–20 mA at 1.0–2.0 ms pulse width at a cycle length of 1000 ms). The phrenic nerves will be paced for 4 min on four occasions during the procedure. Operators are advised to keep the patient in the catheter lab for a minimum of 1 h.

At the end of the procedure once sheaths have been removed all patients will have a three‐way stopcock suture to achieve haemostasis.

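### Section 3.3 ends concealment at sedation, so an operator who knows the arm may perform the cardioversion that both arms share

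*Protocol article*

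**What the plan says.** The rule on concealment is in section 3.3 of the protocol article: "The allocation will remain concealed until after sedation has been achieved at the time of the procedure". The same section writes DCCV into both randomised treatments, conditional on the patient being in AF.

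Section 3.5 (ablation) starts with venous access and continues: "If the patient is in AF then DCCV will be undertaken to cardiovert to sinus rhythm". The coronary sinus catheter and left atrial access come after that. Section 3.6 (sham) also starts with venous access, after which "DCCV will be undertaken if the patient is in AF"; the pacing catheter comes next.

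Section 3.4 separates the procedural team from follow-up and blinds the staff who take over. Section 3.1 has the loop recordings read by an "adjudication committee blinded to patient group". The abstract defines the primary outcome as AF burden at 6 months, "excluding the 3 month blanking period".

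**The concern.** DCCV is background treatment, meant to be equal in both arms so that the comparison isolates PV isolation. It restores rhythm, so it can bear on AF burden directly. The stated limit of concealment is an event that need not come after it. An operator who already knows the arm could, without departing from 3.3, decide how long to persist with cardioversion and when to accept that it has failed.

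If that effort differed by arm, the difference in burden would combine PV isolation with unequal cardioversion. The later safeguards do not reach this step. Blinded follow-up and blinded adjudication protect subsequent care and the reading of recordings, but they cannot change the rhythm in which a patient left the lab. The blanking period removes early data, but a patient left in persistent AF may still be in AF after month 3. A sham-controlled trial is run to exclude performance differences of this kind, so it is worth closing the gap where that costs almost nothing.

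**Working it through.** **1. Order of events.** Setting the sections side by side:

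| Step | Ablation (3.5) | Sham (3.6) |
|---|---|---|
| First | venous access | venous access |
| Second | DCCV if in AF | DCCV if in AF |
| Then | coronary sinus catheter, left atrial access, cryoablation | phrenic nerve pacing |

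The arms diverge only at the third row. Section 3.3 places the end of concealment after sedation. Section 3.4 says only that sedation is given during the procedure and does not place it relative to access or DCCV. Two sequences therefore comply with 3.3:

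- sedation, envelope, access, DCCV, divergence;
- sedation, access, DCCV, envelope, divergence.

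Nothing in the article chooses between them.

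**2. What is fixed about DCCV.** The trigger (being in AF) and the instruction to perform it are the same in both arms. The article does not fix the effort made or the point at which failure is accepted. Only the second can vary with knowledge of the arm.

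**3. The plan's own figures (3.8).** Difference 25 points (50% against 25%), SD 48, two-sided 5% level, 80% power.

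- Normal approximation: n per arm = 2 × (1.960 + 0.842)² × 48² / 25² = 57.9, so 58 per arm and 116 in total.
- Two-sample t-test: 58.84, so 59 per arm and 118 in total, which matches the stated figure.
- Power (normal approximation) is 80.8% with 59 per arm and 86.9% with 70 per arm.

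The time at which the envelope is opened enters none of these.

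**4. Illustrative size.** Shift in the burden contrast = s × d × b, where

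- s = share of patients in AF on the procedure day;
- d = difference between arms in DCCV success caused by knowing the arm;
- b = effect of leaving in sinus rhythm on burden after month 3, in points.

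The documents give none of the three. Table 4 reports persistent AF in 84/105 = 80%, but that is a classification and not rhythm on the day, so 0.8 is used only as the top of the range for s. The ranges for d and b are assumptions.

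| s | d | b | Shift (points) | Share of 25 |
|---|---|---|---|---|
| 0.4 | 0.05 | 10 | 0.2 | 0.8% |
| 0.6 | 0.10 | 30 | 1.8 | 7.2% |
| 0.8 | 0.20 | 50 | 8.0 | 32% |

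The sign is open. Less persistence in the sham arm would enlarge the apparent benefit of PV isolation; less persistence in the ablation arm would shrink it.

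**5. Reach of a change.** The article reports 119 enrolled by April 2023, so 140 − 119 = 21 (15%) were still to be enrolled. It does not say how many of the 119 were still awaiting their procedure.

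**The case against.** The strongest reply is that 3.3 sets only an earliest time. A reader might infer that the envelope is opened before DCCV as a matter of fact. The article does not say so, and a lab that opens it after DCCV is compliant. Section 3.4 also refers to supplementary material on blinding that is not shown, and the full protocol may fix the order. This part of the reply stands, and it limits the point to what the rule permits. It does not remove the point, because the article does state a rule and ties it to an event that need not come after the shared steps.

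Second, DCCV is required on the same criterion in both arms, and no evidence of unequal persistence is offered. That also stands: bias is possible, not shown.

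Third, any carry-over is weakened by the blanking period, by the one DCCV that 3.7 allows in follow-up and by restarted antiarrhythmic drugs, all under blinded care. This is fair, and it is why the lower part of the range is credible. Moreover, b has to be a causal effect. A simple comparison of patients who leave in AF with those who leave in sinus rhythm would overstate it if failed cardioversion marks worse disease.

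Fourth, a reader might infer that failed access or failed DCCV creates a problem of post-randomisation exclusions. The treatment policy estimand in 3.9 does not support this, since such patients stay in their assigned group.

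Finally, the operator must know the arm for the rest of the procedure, so later sealing cannot blind everything done in the lab. That is true, but it is no reason to reveal the arm before a step that does not differ between arms.

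**Conclusion.** The point holds as a weakness in the concealment rule. As written, 3.3 allows an operator who knows the arm to perform the shared DCCV, and the safeguards elsewhere act too late to equalise it. The documents do not support the conclusion that the primary comparison is biased, or that DCCV was delivered unequally.

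Size and direction cannot be derived. The range of 0.2 to 8.0 points, with 1.8 at mid-range, rests wholly on assumed values for the share in AF on the day, the difference in success and the carry-over beyond month 3. Only the most unfavourable combination approaches a third of the planned 25 points. The change is worth making because it is nearly free and cannot be applied to a patient once the envelope is open. The sample size is unaffected.

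**What to change.** In 3.3, state that for patients not yet randomised the allocation stays sealed until sedation, venous access and any DCCV are complete and the resulting rhythm has been recorded. The clinical steps in 3.5 and 3.6, and their order, stay as they are. If the full protocol already fixes this order, bringing 3.3 into line with it is enough.

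For patients already treated, report by arm how many were in AF on the procedure day, how many received DCCV and how many were in sinus rhythm afterwards. This lets a reader judge whether the co-intervention was balanced.

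The cost is one sentence in the protocol and in the lab procedure, one recorded rhythm and one descriptive table, with no added visit, staff or patients. The downside is small: the lab learns the arm, and can prepare arm-specific equipment, a few minutes later. With at most about 21 of 140 patients still to be enrolled in April 2023, and recruitment expected to finish in September 2023, the by-arm report will cover far more patients than the change in sealing.
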